Missing data and attrition will be treated as potential sources of bias, particularly because wartime mobility, distress, and changing access to healthcare may affect follow-up participation. Missingness will first be described by variable, wave, reproductive-status group, recruitment site, and partner-participation status. Intermittent missingness, where participants miss one wave but return at a later assessment, will be distinguished from permanent dropout. Reasons for missingness will be coded where available, including withdrawal, non-response, loss of contact, unsafe contact, relocation, inability to complete the questionnaire, non-consent for clinical-data extraction, and unavailable clinical records. Predictors of dropout will be evaluated using multivariable logistic regression models, and standardized mean differences will be used to quantify imbalance between retained and non-retained participants. Models will use full-information maximum likelihood estimation under a missing-at-random assumption (142). Missing covariates will be handled using multiple imputation by chained equations (RRID: SCR_026363), with estimates pooled using Rubin’s rules (143–145). Sensitivity analyses will be used to assess the robustness of primary findings. These will include complete-case analyses, inverse probability-of-censoring weighting based on estimated probability of follow-up retention, and alternative imputation specifications that include baseline distress, war-related exposure, displacement, reproductive status, and recruitment site as predictors of missingness. Where dropout appears related to psychological distress or other outcome-related variables, additional sensitivity analyses will compare primary model estimates before and after applying retention weights and after restricting analyses to participants with at least two completed waves. If results differ materially across these specifications, conclusions will emphasize the direction, size, and robustness of effects rather than a single model estimate. Baseline analyses will first be conducted for the total sample and separately by reproductive-status group. Group differences at baseline will be examined to characterize cohort heterogeneity and to identify variables requiring adjustment in longitudinal models.

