More broadly, the protocol should be interpreted in light of the general limitations of ambitious longitudinal observational studies conducted under unstable conditions. Wartime and displacement contexts may affect who is reachable, who is able or willing to participate, and who remains in follow-up. Attrition over 12 months is likely to be a major methodological challenge, particularly in the context of war, mobility, and changing contact circumstances. The protocol addresses this through sample-size planning and flexible follow-up procedures, which is a strength, but loss to follow-up may still reduce statistical precision and introduce bias if discontinuation is associated with distress, instability, or service access. In addition, although the study includes several established instruments, some Ukrainian-language versions are newly translated or still undergoing psychometric evaluation. Interpretation of the eventual findings will therefore need to take measurement performance into account.

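### No named missing-data check lets dropout depend on unrecorded distress at the missed wave, so agreement among them would not show that the 12-month WHO-5 contrast is robust to it

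*Protocol article*

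**What the plan says.** All of the following is in the Protocol article.

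- **Recognised risk.** Section 2.5 warns that "wartime mobility, distress, and changing access to healthcare may affect follow-up participation". Section 3.2 repeats that loss to follow-up may "introduce bias if discontinuation is associated with distress, instability, or service access".
- **Primary estimation.** "Models will use full-information maximum likelihood estimation under a missing-at-random assumption" (Section 2.5).
- **Standing sensitivity analyses.** "These will include complete-case analyses, inverse probability-of-censoring weighting based on estimated probability of follow-up retention". A third check varies the imputation model by adding observed predictors, among them distress at baseline, stressor exposure and site.
- **Triggered analyses.** "Where dropout appears related to psychological distress or other outcome-related variables", the plan adds two things: "additional sensitivity analyses will compare primary model estimates before and after applying retention weights", and a restriction to women who completed two or more waves.
- **Target.** The principal test is the interaction of baseline stressor burden with time on WHO-5, and change from baseline to 12 months is the principal contrast (Section 2.5). Burden is a count of endorsed stressor domains (Section 2.4.1.1).
- **Expected loss.** Section 2.2.1 plans for 73.0% retention at 12 months, or 52% in the conservative scenario.

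The article names no delta-adjusted, pattern-mixture, selection, shared-parameter or tipping-point analysis.

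**The concern.** The article does more than leave missing-data detail for later. It states what will be done if dropout looks related to distress or the outcome, and that response does not relax the assumption such dropout puts in doubt. A retention weight can depend only on what was recorded. If a woman's well-being falls after her last completed wave and she leaves for that reason, her weight and her imputed value both miss the fall.

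The study's own procedures make this route plausible. Section 2.2.2 allows an assessment to be put off when a participant is acutely distressed, and Section 2.6.1 lets her stop or pause once a distress threshold is crossed. Whether that loses the WHO-5 depends on item order and later completion, which the article does not give.

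At stake is the reading of the principal result. If unseen 12-month scores are worse than predicted, and dropout is heavier at higher burden, the contrast is pulled towards no harm. The named analyses could agree with each other and all be wrong together.

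**Working it through.** **1. What each named analysis assumes**

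| Analysis | Condition for validity | Models unseen scores that depart from MAR? |
|---|---|---|
| Full-information maximum likelihood (primary) | MAR | No |
| Retention (censoring) weights | MAR given the weight predictors | No |
| Alternative imputation predictors | MAR given more observed data | No |
| Complete case | Stricter than MAR | No |
| At least two waves | Stricter than MAR for the selection step | No |

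**2. How much recorded scores say about a missing one**

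The planning correlation is AR(1) with parameter 0.38 (Section 2.2.1). An adjacent wave explains 0.38² = 0.144 of the variance. The baseline-to-12-month correlation over three steps is 0.38³ = 0.055. On the plan's own figure, earlier WHO-5 is a weak proxy for the missing 12-month score.

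**3. The plan's sample size, as a yardstick**

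The 328 cannot be reproduced, because the article states no effect size and no wave-specific SDs. It can be back-solved from N per group = 2φ(z₀.₉₇₅ + z₀.₈₀)²SD²/δ², with common SD 1.05, AR(1) 0.38 and retention 1, 0.929, 0.842, 0.73.

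- For the change contrast with equally spaced waves, φ = 2.2313. Then δ = 0.485, or 0.485/1.05 = 0.462 SD.
- Under the conservative retention, φ = 2.7312. Power at 328 is 0.716 and N for 80% power is 402. With 0-3-6-12 month spacing these become 0.713 and 406. The plan states about 70% and 416, so the yardstick is close enough to use.
- In the conservative scenario, the contrast detectable with 80% power is 0.462 × √(2.7312/2.2313) = 0.511 SD.

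**4. Women with no 12-month score**

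328 × 0.27 ≈ 89; conservative 328 × 0.48 ≈ 157.

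**5. Bias under assumed inputs**

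Let p be the share missing at 12 months and d the distance by which unseen scores fall below their MAR prediction, in the higher (H) and lower (L) burden groups. Then bias = p_H·d_H − p_L·d_L. With a common d it is (p_H − p_L)·d.

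- Main scenario, assumed 35% and 19% (mean 27%): 0.16 × 0.25, 0.50, 0.75 = 0.04, 0.08, 0.12 SD. This is 9% to 26% of 0.462.
- Conservative scenario, assumed 58% and 38% (mean 48%): 0.20 × the same = 0.05, 0.10, 0.15 SD. This is 10% to 29% of 0.511.
- With p_H = p_L and d_H = d_L, the bias is 0.

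**6. Illustrative simulation**

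Settings, all assumed apart from the 0.38 and the overall retention: 200,000 women, two burden groups, SD units, AR(1) 0.38, about 73% retained at 12 months, true contrast about −0.35 SD. The log-odds of dropout rise by 1.5 per SD of lower well-being at higher burden and by 0.3 at lower burden. Dropout depends either on the last recorded score or on the unseen current one.

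| Analysis | Dropout on recorded score (truth −0.349) | Dropout on unseen score (truth −0.353) |
|---|---|---|
| Full-information likelihood | −0.350 | −0.122 |
| Retention weights | −0.350 | −0.122 |
| MAR imputation | −0.347 | −0.120 |
| Complete case | −0.423 | −0.161 |
| At least two waves | −0.445 | −0.161 |
| Delta-adjusted imputation, true shift supplied | −0.349 | −0.353 |

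In the right-hand column, retention was 63.5% and 82.5% (higher, lower burden), with shifts of −0.71 and −0.15 SD. The formula in step 5 gives 0.365 × 0.71 − 0.175 × 0.15 = 0.233, and −0.353 + 0.233 = −0.120, which matches the imputation result.

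The five planned types span 0.041 SD where all are badly wrong and 0.098 SD where the primary model is right. In this setting, closeness among them carries no reassurance.

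**7. Why shifts must go both ways**

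Lowering only higher-burden dropouts can only enlarge apparent harm. To bring an assumed MAR estimate of −0.35 SD to zero, missing higher-burden scores must move up by 0.35/0.27 = 1.30 SD, or 0.35/0.48 = 0.73 SD, taking the overall loss as that group's loss. Statistical significance would go earlier.

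**The case against.** The strongest reply is that distress-related dropout is not the same as dropout outside MAR. Table 3 schedules WHO-5, GAD-7, IES-R and SCI-2-SF for all women at every wave. Dropout can only appear distress-related through recorded distress, and for that, likelihood and weights are a sound response. The left-hand simulation column bears this out. This stands, and it limits the point to new distress at the missed wave.

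Four stronger readings are tempting, and the documents do not support them:

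- That the plan expects distress-driven dropout. It says only that distress may affect participation.
- That every check assumes MAR. The complete-case and two-wave analyses do not rest on MAR as such; they need stricter conditions.
- That exposed or distressed women are known to be likeliest to leave. No section says so.
- That the authors would take agreement as ruling out informative dropout. They give a rule for divergent results only, and Section 3.2 concedes that "loss to follow-up may still reduce statistical precision and introduce bias if discontinuation is associated with distress, instability, or service access".

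It is also fair that the list of analyses is open-ended, that an analysis plan not shown may add to it, and that the bias figures come wholly from assumed inputs. The simulated dropout is strong, and it uses two groups where the primary exposure is a count. These points reduce the weight of the numbers. They do not remove the gap, because the article itself sets out the response to outcome-related dropout and that response contains no departure from MAR towards unseen outcomes.

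**Conclusion.** The concern holds in limited form. The named analyses cover dropout explained by recorded distress. None can test dropout that depends on unrecorded WHO-5 at the missed wave and differs by stressor burden, so their agreement would not establish robustness for the principal contrast. That contrast sits where loss is greatest: 27% planned, 48% conservative.

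Under the assumed differences in dropout (16 to 20 points) and shifts (0.25 to 0.75 SD), the bias is 0.04 to 0.15 SD, roughly a tenth to just under a third of the contrast the study can detect. It would be larger if the shift were also greater at higher burden, and zero if neither dropout nor shift differed. The size is illustrative; the structural gap does not depend on it. This should be changed, but it does not invalidate the primary model.

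**What to change.** Add one prespecified delta-adjusted (pattern-mixture) multiple imputation of missing post-dropout WHO-5:

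- Shift imputed values in both directions, for example −0.75 to +0.75 SD in steps of 0.25.
- Apply the shifts to all dropouts, to higher-burden dropouts only, and to lower-burden dropouts only, or let the shift vary with baseline burden.
- Keep burden as the count used in the primary model. Any cut serves only to say which dropouts are shifted.
- Report the shift at which the burden-by-12-month contrast changes conclusion, or state that none in the range does and give the estimates at both ends.
- State that the retention-weight and two-wave analyses do not address dropout that depends on unobserved WHO-5.

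The cost is one extra analysis on data already collected, extending the multiple imputation already planned for covariates to the missing outcome. Its results rest on assumed shifts, so it should be labelled as sensitivity only.

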#### Sample size

2.2.1

The sample size was estimated for the primary longitudinal mixed-model repeated-measures analysis, with the World Health Organization–Five Well-Being Index (WHO-5) score anchored as the primary outcome. Accordingly, the calculation was designed to provide adequate statistical power to detect differences in longitudinal WHO-5 trajectories according to war-related stress exposure. Sample size estimation was conducted in R (RRID: SCR_001905) using the *longpower* package (80). Parameter values were derived from previously published longitudinal studies, consistent with Harrall et al.’s recommendations (81). Given the substantial logistical and participant burden associated with data collection during an ongoing war, statistical power was set at 0.8, and the type I error rate was set at 0.05. Equal allocation across the two comparison levels specified in the power model was assumed.

The standard deviation of the WHO-5 outcome among postpartum women was set at 1.05, based on data reported by Mor et al. (82). The correlation structure was specified as a first-order autoregressive process with a correlation parameter of 0.38, informed by longitudinal data reported by Qandil et al. (83). Retention assumptions were based primarily on the cumulative follow-up pattern reported by Damtew et al. (84), with retention rates of 92.9% at 6 weeks, 84.2% at 6 months, and 73.0% at 12 months, calculated using the baseline cohort as the denominator at each follow-up. Although some studies in post-conflict settings have reported relatively high retention, such as the 77.3% 2-year retention reported by Silove et al. (85), the present assumptions were considered more appropriate for this study context.

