The final sample size calculation assumed a heterogeneous first-order autoregressive variance-covariance structure, four measurement occasions, and a two-sided test. Under these assumptions, the minimum required sample size was estimated at 328 participants. This sample size is expected to provide adequate power for detecting differences in longitudinal WHO-5 trajectories by war-related stressor exposure in the primary mixed-model repeated-measures analysis after accounting for attrition. The sample-size calculation was anchored to the WHO-5 score as the reference outcome for the primary longitudinal analysis in the women’s cohort. Secondary outcomes, for instance, reproductive-behavior outcomes, clinical outcomes, reproductive-status-by-time interactions, and the optional dyadic partner component will be analyzed where the available data structure, sample size, and model stability permit. These analyses will not be considered independently powered confirmatory tests; they will be interpreted as hypothesis-generating.

A sensitivity power analysis was also conducted using a more conservative compounded attrition scenario, assuming 85% retention per 3-month intervals up to the 12-month follow-up, to reflect the possibility of greater attrition in the wartime context. In this scenario, retention proportions were set at 1.00, 0.85, 0.72, and 0.52. Under this conservative attrition scenario, the planned sample size of N = 328 would provide approximately 70% power, which was considered relevant for a perinatal population in a wartime setting (86). To maintain 80% power under the same conservative retention assumptions, the required sample size would increase to approximately N = 416. Accordingly, the planned sample size should be interpreted as adequately powered for the primary longitudinal model under the main retention assumptions, whereas findings should be interpreted more cautiously if attrition approaches the conservative scenario. The corresponding R script is available in the project Open Science Framework (RRID: SCR_003238) repository (87).

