Item-level analyses will include inspection of response distribution and missingness, floor and ceiling effects, corrected item-total correlations, and score distributions. For measures administered at multiple assessment waves, longitudinal measurement invariance will be evaluated to assess whether the constructs are measured comparably over time. Invariance by respondent characteristics or reproductive status will be examined where item wording, sample size, and model stability permit. Configural, metric, and scalar invariance will be examined sequentially; partial invariance will be considered when full invariance is not supported (146).

The results of these analyses will inform the interpretation of scale scores, between-group comparisons, and longitudinal change estimates. If a translated scale demonstrates poor psychometric performance, substantive analyses using that scale will be reconsidered before interpretation. The research team will inspect item wording, response distributions, factor loadings, residual correlations, reliability estimates, and the effect of individual items on model fit and internal consistency. Depending on the source and extent of the problem, analyses may use theoretically justified subscale scores, conduct sensitivity analyses excluding items, or report the measure descriptively. Measures with inadequate reliability, unstable factor structure, or insufficient evidence of comparability across groups or time will not be used. Any deviations from the planned scoring approach will be reported transparently.

Primary outcomes will be analyzed using mixed-effects growth models with repeated observations nested within participants. Models will include fixed effects for time, war-related stress exposure, and the interaction between them. Time will initially be modeled as categorical; alternative specifications will be compared when empirically justified. Random intercepts will be used to estimate between-person differences in baseline symptom levels, and random slopes for time will be tested to capture heterogeneity in change over time. Model selection will be guided by likelihood-ratio tests, Akaike information criterion, Bayesian information criterion, convergence diagnostics, and variance estimates. The intraclass correlation coefficient will be estimated from unconditional models.

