Recruitment through healthcare institutions should likewise be viewed in balanced terms. Clinic-based recruitment provides access to women currently navigating reproductive or perinatal care and increases the practical relevance of the study to real-world service settings. It also facilitates linkage, where consent is provided, between self-report and routine clinical data. However, healthcare-based sampling may under-represent women whose contact with services is reduced or interrupted, including those affected by displacement, financial barriers, safety concerns, or disengagement from care. In a wartime setting, this is especially important because uneven access to care may itself form part of the exposure context. The findings will therefore need to be interpreted with awareness that women outside formal care pathways may not be fully represented.

Several methodological limitations inherent to the prospective cohort design should also be acknowledged. Although repeated assessments allow temporal ordering of exposures and outcomes, the observational nature of the study precludes causal inference in the experimental sense. Associations between war-related exposures, reproductive transitions, and mental-health outcomes may be influenced by unmeasured or imperfectly measured confounders, including prior trauma exposure, pre-war mental health, access to care, social support, and changing local security conditions. In addition, reproductive status may change during follow-up, and the timing of these transitions may not be uniform across participants.

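### The primary WHO-5 model has no term for recruitment site and leaves its within-woman covariance open, so the standard error of the burden-by-12-month contrast could be too small.

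*Protocol article*

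**What the plan says.** Data analysis (2.5) sets the level of nesting: "Primary outcomes will be analyzed using mixed-effects growth models with repeated observations nested within participants". The same section repeats the participant-level nesting when it describes the women's cohort. Random intercepts are planned, random slopes for time are to be tested, and likelihood-ratio tests, AIC, BIC, convergence and variance estimates guide the choice. On the form of time: "Time will initially be modeled as categorical; alternative specifications will be compared when empirically justified".

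The section also fixes the outcome (WHO-5), the exposure (baseline stressor burden), the test (burden by time) and the principal contrast (baseline to 12 months). It rules out stepwise selection for primary inference.

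Sample size (2.2.1) plans for a mixed-model repeated-measures analysis: "The final sample size calculation assumed a heterogeneous first-order autoregressive variance-covariance structure, four measurement occasions, and a two-sided test". Its inputs include "first-order autoregressive process with a correlation parameter of 0.38".

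Recruitment runs through healthcare institutions in Ukraine (Study design, 2.1). Recruitment site is recorded. It is used to describe missingness, in alternative imputation models, and as an optional adjustment where completeness of clinical data differs between sites. No site effect or cluster-robust standard error is named for the primary model. Strengths and limitations (3.2) lists "changing local security conditions" among the possible confounders.

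**The concern.** There are two separate issues.

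**Site.** The burden score counts domains that include displacement, disrupted access to care and nearness to hostilities (2.4.1.1). Women attending one hospital are likely to resemble each other on these. They may also share local events that move WHO-5 over follow-up. When exposure and change in outcome both cluster by site, a model that treats women as independent overstates the information on their association. A random slope for each woman does not absorb dependence between women.

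**Covariance.** A random intercept alone implies the same correlation at every lag. The planning assumption has correlation decaying with lag. The principal contrast spans the longest lag, where the two assumptions differ most. If the analysis ends with a random intercept only, the model credits baseline and 12 months with more correlation than the planning value allows, and the standard error of the change is too small.

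At stake is the type I error and interval coverage of the one test on which the primary hypothesis rests.

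**Working it through.** **Inputs from Sample size (2.2.1).** Two-sided alpha 0.05, power 0.80, AR(1) correlation 0.38, SD 1.05, main retention 1, 0.929, 0.842, 0.730 over the four waves (its 6-week figure is taken for the 3-month wave), N = 328. For the covariance check the SD is set to 1, since it cancels from the ratios. The correlation is applied per wave.

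**The plan's own figure.** N = 328 cannot be reproduced directly, because the article states no effect size. Solving backwards for a 12-month change contrast between two equal groups:
- Variance factor of the change under main retention: 2.231.
- delta = sqrt(4 × (1.960 + 0.842)² × 2.231 / 328) = 0.46 SD.
- With the conservative retention (1.00, 0.85, 0.72, 0.52) the factor is 2.731, which gives about 72% power at N = 328 and N of about 402 for 80% power. The article states about 70% and 416, so this is close but not exact.

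**Covariance.** AR(1) at 0.38 gives a baseline-to-12-month correlation of 0.38³ = 0.055. Fitting each simpler structure to that truth under main retention, and comparing the variance it reports for the change contrast with the true variance of its estimate:

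| Fitted structure | Reported | True | SE ratio | Error of a 5% test |
|---|---|---|---|---|
| Random intercept only | 1.818 | 2.256 | sqrt(1.818/2.256) = 0.898 | 2 × (1 − Φ(1.96 × 0.898)) = 7.8% |
| Random intercept plus linear slope | 2.382 | 2.236 | 1.032 | 4.3% |

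The random-intercept fit imposes a common correlation of about 0.26 at all lags. Spacing the AR(1) by months instead of waves gives an SE ratio of about 0.91 and an error of about 7.5% for the intercept-only model.

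In 1,000 simulated studies (N = 328, main retention, no site effect), a likelihood-ratio test for a linear slope kept the slope in 99.9%. The error of the selected model was 3.4%.

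**Why the slope might still be dropped.** The text does not say the slope is linear, and time starts as categorical. Taken literally, random effects for categorical time mean four per woman: 10 variances and covariances plus a residual variance, so 11 parameters for a 4 × 4 matrix with 10 distinct elements. That is not identified. Expected observations are 328 × (1 + 0.929 + 0.842 + 0.730) = about 1,148, against 328 × 4 = 1,312 random effects. Under a convergence rule, the analyst could end with the intercept-only model.

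**Site.** The article gives neither the number of sites nor any ICC, so these are assumptions. Design effect = 1 + (m − 1) × ICC of exposure × ICC of change, with m = 328 / sites. Error = 2 × (1 − Φ(1.96 / sqrt(design effect))).

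| Sites (m) | ICC exposure, ICC change | Design effect | SE ratio | Error by formula | Simulated error, slope selected by test |
|---|---|---|---|---|---|
| 20 (16.4) | 0.1, 0.01 | 1 + 15.4 × 0.001 = 1.02 | 0.99 | 5.2% | 4.0% |
| 10 (32.8) | 0.3, 0.02 | 1 + 31.8 × 0.006 = 1.19 | 0.92 | 7.3% | 5.7% |
| 5 (65.6) | 0.5, 0.05 | 1 + 64.6 × 0.025 = 2.6 | 0.62 | about 22% | 15.1% |

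The simulated values are lower partly because the slope model is itself slightly conservative under AR(1). With 1,000 trials the Monte Carlo standard error near 5% is about 0.7 points, so 5.7% cannot be told apart from nominal.

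**The case against.** The strongest case against runs as follows.

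- **The plan tests a random slope.** With a linear slope the error is at or below nominal, and the slope would nearly always be kept. This stands. A reader might infer that the planning correlation by itself makes the primary standard error too small. The document does not support that, because the shortfall needs the slope to be dropped.
- **The analysis is prespecified where it matters most.** Outcome, exposure, interaction and 12-month contrast are fixed, and stepwise selection is barred. This also stands. A reader might infer that the primary test as a whole is chosen after the fact. Only the covariance and the form of time are open. A move to linear time would matter, though, because the interaction would become a slope and no longer the wave-specific 12-month contrast.
- **Site handling may sit in a separate analysis plan.** This is partly fair, since the article is condensed and refers to contextual covariates. But it states the nesting level twice, lists the model's fixed effects and assigns site other uses. The model as stated has a gap that is worth closing.
- **The site effect may be small.** Enrolment is rolling, so local events do not line up with waves. Several domains are largely individual, and women may relocate. At 73% retention the 12-month cluster is smaller: with 10 sites, m is about 24, and ICCs of 0.4 and 0.05 give 1 + 22.9 × 0.02 = 1.46, against 1.64 at full size. This stands as a reason not to quote a single inflated error rate.

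**Conclusion.** The site point holds as a weakness of unknown size. The stated model ignores a clustering level that the study records and that its exposure plausibly follows. Over the assumed range the design effect is about 1.02 to 2.6, and simulated error ran from 4.0% to 15.1%. It becomes serious only with few sites and strong clustering of both exposure and change. The article contains nothing that narrows this range, so no particular type I error can be claimed.

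The covariance point holds conditionally. The power model and the analysis model differ. With a linear random slope the error is about 4.3%. With a random intercept only, the standard error is about 10% too small and the error about 8%. These figures rest on AR(1) at 0.38 with equal variances, main retention and monotone dropout.

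Both points call for fixing the model in advance. Neither shows that the planned result would be wrong.

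**What to change.** State one primary model before data are seen:

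- WHO-5 with wave as categorical, burden, burden by wave and baseline reproductive status.
- Unstructured within-woman covariance (10 parameters, with AR(1) as a special case), or heterogeneous AR(1) to match the power model, with a named fallback if it does not converge.
- Site handled either by a random site effect that extends to change over time, or by cluster-robust standard errors with a small-sample correction. A site intercept alone is not enough, because it largely cancels from a within-woman change.
- The one-degree-of-freedom burden-by-12-month contrast as the decision test.

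Keep the growth models and alternative time forms as supportive analyses. Give the expected number of sites.

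The cost is a change of wording. Intervals will be somewhat wider. If sites are few, a random site-by-time effect may be hard to estimate and the small-sample correction will matter.
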